### Study outcomes

Participants visit the study center for assessments at baseline, 12 weeks, and 24 weeks (wait list control group only), with 12 weeks being the primary time point. Patient-reported outcomes are assessed using online questionnaires, which participants either receive via Castor EDC shortly prior to the study center visit or complete during their visit, prior to the physical tests. Patient-reported outcomes are also assessed remotely at 6 weeks, 18 weeks (wait list control group only), 24 weeks (intervention group only), and 36 weeks. Additionally, participants receive phone calls at these time points to collect information on potential (serious) adverse events ((S)AEs), changes in medication, and health status (e.g., cancer recurrence). During the in-person visits, anthropometrics and physical fitness/performance are assessed and blood samples are drawn. To inform whether the intervention could be delivered entirely live-remote in routine clinical practice, we assess if live-remote testing is also feasible. Therefore, we perform live-remote physical fitness and function testing in all wait list control participants at 12 and 24 weeks as well.

Socio-demographic data are assessed at baseline with a study-specific questionnaire. Medical data are based on patient-report or retrieved from medical records. Personal data are coded and all data are handled in compliance with the General Data Protection Regulation (GDPR) (EU) 2016/679. Validity of the data is checked by an independent monitor.

### Primary outcomes

The LION-RCT has two primary outcomes: HRQoL and the participant’s most burdensome side effect (i.e., cancer-related fatigue, emotional distress, low physical functioning, or CIPN).

#### HRQoL

HRQoL is assessed with the core questionnaire of the European Organization for Research and Treatment of Cancer (EORTC) that has been developed and validated for assessing HRQoL in patients with cancer (EORTC QLQ-C30). The summary score, which includes all original EORTC QLQ-C30 subscales excluding the global QoL score and financial difficulties score, is used as primary outcome [26, 27]. Scores range from 0 to 100 with a higher score indicating a better HRQoL.

#### Most burdensome side effect

The following questionnaires will be used to assess the side effects. Details on how the scores will be combined are provided in the statistical analyses section.

Cancer-related physical fatigue is assessed with the EORTC QLQ-FA12 questionnaire [28]. This is a 12-item questionnaire that assesses different dimensions of cancer-related fatigue. We use the physical fatigue dimension as primary outcome. Scores range from 0 to 100 with a higher score indicating higher levels of physical fatigue. Emotional distress is assessed with the Patient Health Questionnaire Anxiety and Depression Scale (PHQ-ADS) [19], which combines the 9-item Patient Health Questionnaire depression scale (PHQ-9) and 7-item Generalized Anxiety Disorder scale (GAD-7). A composite score, ranging from 0 to 48, is used to assess the overall burden of anxiety and depression, with a higher score indicating a higher burden.

Physical functioning is measured using the 5-item EORTC QLQ-C30 physical functioning scale. To increase reliability for use in patients with higher levels of physical functioning, five items from the EORTC questionnaire item bank were added to the physical function scale (see *Additional file 2* for the specific items). A domain-specific T-score will be calculated using the EORTC software and including all ten items. This T-score reflects the score of the participant relative to an age- and gender-matched European reference population, with 50 representing average physical functioning.

CIPN is assessed using the EORTC QLQ-CIPN20 questionnaire, which consists of 20 items addressing symptoms and the functional impact of CIPN [29]. A sum score of items 1–18, ranging from 0 to 100, is used to assess the overall CIPN burden, with a higher score indicating more severe symptoms [30].

The primary outcomes are assessed at all time points using the above-mentioned questionnaires. The same questionnaires are used to ascertain eligibility, except for CIPN (2 PRO-CTCAE items). Therefore, at baseline, they are only completed once, if the time window between eligibility screening and the baseline visit is less than 4 weeks. If the time window between eligibility screening and the baseline visit is more than 6 weeks, the participants are asked to repeat the questionnaires (Table 3).

**Table 3 Tab3:** Overview of all assessments in the LION-RCT

		T0	T1	T2	T3	T4	T5
**Outcomes**	**Instrument**	Baseline	6 wks	12 wks	18 wks	24 wks	36 wks
**Primary outcomes**							
**Health-related quality of life**	EORTC QLQ-C30	X	X	X	X (WCG)	X	X
**Cancer-related fatigue**	EORTC QLQ-FA12	X	X	X	X (WCG)	X	X
**Emotional distress**	Patient Health Questionnaire Anxiety and Depression Scale (PHQ-ADS)	X	X	X	X (WCG)	X	X
**Physical function**	Modified from EORTC QLQ-C30	X	X	X	X (WCG)	X	X
**Chemotherapy-induced peripheral neuropathy**	EORTC QLQ-CIPN20	X	X	X	X (WCG)	X	X
**Secondary outcomes**							
**Patient-reported outcomes**							
**Sleep**	Pittsburgh Sleep Quality Index (PSQI)	X		X		X	X
**Pain**	Items from EORTC QLQ-SURV100	X		X		X	X
**Cognitive functioning**	2 subscales of FACT-Cog	X		X		X	X
**Body Image**	Body Image Scale	X		X		X	X
**Fear of recurrence**	Subscale of EORTC QLQ-SURV100	X		X		X	X
**Work limitations**	Work Limitations Questionnaire (WLQ)	X		X		X	X
**Self-reported physical activity**	Modified version of the GODIN questionnaire	X		X		X	X
**Quality adjusted life years**	EQ-5D-5L	X		X		X	X
**Healthcare resource consumption**	Medical Consumption Questionnaire (iMCQ)	X		X		X	X
**Productivity loss**	Productivity Cost Questionnaire (iPCQ)	X		X		X	X
**Satisfaction with the exercise program**	Self-developed questionnaire			X (IG)		X (WCG)	
**Participant insights**	Concept mapping			X (IG)		X (WCG)	
**Physical measurements (in-person)**							
**Functional performance**	Single leg stance^a^, Timed Up and Go Test	X		X		X (WCG)	
**Physical fitness**	Steep Ramp Test (SRT), Chester Step Test, 30 s sit-to-stand test, handgrip strength test, h1-RM chest- and leg press, isokinetic and isometric peak torque^b^	X		X		X (WCG)	
**Measured physical activity**	Physical activity tracker (Fitbit Inspire 3)	X	X	X	X	X	X
**Anthropometry**	Body weight, height, waist-to-hip ratio	X		X		X (WCG)	
**Resting heart rate and blood pressure**	-	X		X		X (WCG)	
**Body composition**	Bio-impedance^c^	X		X		X (WCG)	
**Blood markers**	Plasma, serum and white blood cell count	X		X			
**Physical measurements (live-remote)**							
**Functional performance**	Single leg stance, Timed Up and Go Test			X (WCG)		X (WCG)	
**Physical fitness**	Chester Step Test, 30 s sit-to-stand test, push-up test and plank position holding time test			X (WCG)		X (WCG)	
**Socio-demographical and clinical data**							
**Socio-demographics**	Self-developed questionnaire	X					
**Social support**	Index of Sojourner Social Support (ISSS)	X					
**Self-efficacy**	General Self-efficacy Scale	X					
**Cancer characteristics and treatment history**	Medical records, self-report	X					
**Medical history and concomitant diseases**	Medical records, self-report	X					
**Concomitant medication**	Medical records	X	X	X	X	X	X
**Exercise-related adverse events**	Reports of participants, exercise professionals, or medical records	X	X	X	X	X	X

*IG* intervention group, *WCG* wait list control group

^a^This test is performed on a force plate at AICSO and UKHD/DKFZ.

^b^This test is performed at UKHD/DKFZ only.

^c^This test is performed at UMCU, NKI, UKHD/DKFZ, DSHS, AICSO, ONK, CAB only.

### Secondary outcomes

#### Patient-reported outcomes

Secondary outcome measures comprise the EORTC QLQ-C30 function and symptom scales, and the other fatigue dimensions of the EORTC QLQ-FA12 (emotional, cognitive, and total fatigue scores). We extended the social and role functioning scales of the EORTC QLQ-C30 by 2 items from the EORTC item bank (see *Additional file 2* for the specific items). Sleep problems are assessed using the Pittsburgh Sleep Quality Index (PSQI), which contains 19 self-reported items assessing subjective sleep quality, sleep latency, sleep duration, habitual sleep efficiency, sleep disturbances, use of sleeping medication, and daytime dysfunction over the past month [31]. In addition to the general pain score of the EORTC QLQ-C30, pain (i.e., joint and muscle pain) is evaluated using two specific items from the EORTC Survivorship questionnaire (EORTC QLQ-SURV100; see *Additional file 2*) [32]. These items are scored on a scale from 0 to 100, with higher scores indicating more pain, and will be analyzed separately. Fear of recurrence is assessed using five specific items from the EORTC QLQ-SURV100 (see *Additional file 2*). These items are summarized into two scores, health distress and symptom awareness, with a score ranging from 0 to 100 and a higher score indicating more fear of recurrence. Cognitive functioning is assessed with two subscales of the Functional Assessment of Cancer Therapy–cognitive functioning questionnaire (FACT-cog) [33]. The “Perceived Cognitive Impairment” subscale includes 20 items with a score ranging from 0 to 80. The “Impact on QoL” subscale includes 4 items with a score ranging from 0 to 16. A higher score indicates a better QoL. The 25-item Work Limitation Questionnaire (WLQ) assesses the extent to which health problems affect specific aspects of job performance and its impact on productivity [34]. An overall WLQ-index score can be calculated. This score ranges from 0 to 100 with a higher score indicating more impact of health problems on productivity. Body image is assessed using the 10-item Body Image Scale (BIS) [35]. A total score can be calculated, ranging from 0 to 30 with a higher score indicating more body image distress.

#### Physical activity

Self-reported physical activity levels are measured using the Modified Godin-Shephard Leisure Time Exercise Questionnaire, which consists of four items that assess the average frequency and duration of mild, moderate, and vigorous intensity aerobic activities, as well as moderate-to-vigorous intensity resistance exercises performed in bouts of at least 10 min during leisure time in a typical week [36, 37]. In addition, questions were added about exercise types and settings. The activity tracker is used to measure step count, heart rate, and physical activity minutes. Participants in both the intervention and wait list control group are instructed to wear the activity tracker throughout the study period, but at least during the 7 days following randomization and the 7 days preceding the 12-week, 24-week, and 36-week post-baseline assessments. Additionally, participants are asked to wear the activity tracker during live-remote exercise sessions and physical fitness testing.

#### Anthropometrics

Anthropometric data (i.e., body weight, height, waist-to-hip ratio) are measured in lightweight clothing without shoes.

#### Body composition

As add-on measurement, body composition (fat mass and fat free mass) is assessed in some centers using a whole body/segmental bio impedance analysis (BIA). Measurements are taken in a fasted state (no enteral intake for a minimum of 2 h), with an empty bladder, in a standing or lying position. BIA devices may differ between centers, but participants within each center are consistently measured on the same device.

#### Resting heart rate and blood pressure

Resting heart rate and blood pressure are measured in a seated position prior to the physical measurements.

#### Blood markers

Blood sampling is performed by vein puncture at baseline and 12 weeks post-baseline. Plasma and serum are derived from whole blood samples. Less than 30 ml of blood is collected per visit. In the 24 h prior to blood sampling, participants are instructed not to exercise vigorously or drink alcohol, and in the 2 h prior to blood sampling, they are asked to abstain from cigarettes, food, and drinks. Immediately after collection, a proportion of the blood sample is analyzed to assess full blood count indices such as leukocytes, hemoglobin, and C-reactive protein. The remaining blood is centrifuged and stored at < −70 °C at the local laboratories according to standardized procedures. Blood samples are transferred to the central biobank at the KI for analysis after the last sample has been collected locally.

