**Fig. 1 Fig1:**
[figure not shown]
Recruitment and LION-RCT procedures

To be eligible for the study, potential participants have to score above the threshold (Table 2) for at least one of the targeted side effects. Individuals who do not score above the threshold for any of the side effects are provided with country-specific resources related to exercising following a cancer diagnosis. Individuals who score above the threshold for multiple side effects meet with a member from the local research team to identify their most burdensome side effect through a shared decision-making process. Following this process, eligible participants are invited for their baseline visit (i.e., assessment of anthropometrics and physical fitness/performance, and blood draw).

**Table 2 Tab2:** Pre-defined cut-off values for the side effects

**Side effect**	Questionnaire	Cut-off value
**Fatigue** [18]	EORTC QLQ-C30 fatigue symptom scale	> 39
**Emotional distress** [19]	PHQ-ADS	≥ 20
**Physical function** [18]	EORTC QLQ-C30 physical function scale	< 83
**CIPN**^**a**^** [**20]	PRO-CTCAE^b^	> 0

^a^Participants need to have been exposed to neurotoxic chemotherapy

^**b**^This questionnaire is used for eligibility screening only

After the baseline visit, participants are randomly allocated (1:1) to either the intervention or wait list control group by central computerized randomization using a blocked computer-generated sequence, effectively concealing the random allocation sequence. Castor EDC®, a cloud-based clinical data management platform, is used for randomization and data capture. Randomization is stratified by the participant’s most burdensome side effect, country and sex. Due to the nature of the intervention, blinding of participants and the study team to intervention assignment is not possible. However, data analysts will remain blinded to group allocation until the primary analyses have been completed. Participants randomized to the intervention group receive exercise instructions and an exercise kit at the end of their baseline visit. This kit includes the necessary exercise equipment to set-up their home exercise space: gym mat, dumbbell set with adjustable weights, resistance bands and an aerobic stepper. The wait list control group receives this kit 12 weeks post-baseline. All participants receive an activity tracker (Fitbit) at baseline.

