#### Base module—HRQoL

The base module is based on the recent ACSM exercise guidelines for cancer survivors [7]. Each session starts with a 5–10 min warm up, consisting of mobilization and light intensity aerobic exercises. The warm-up is followed by 30 min of resistance training, during which seven to eight exercises that target the major muscle groups are performed using either one’s own body weight, dumbbells or resistance bands. Two sets of 8–12 repetitions per exercise are performed at moderate-to-vigorous intensity (rate of perceived exertion (RPE) 13–17). Each time the maximum number of repetitions is reached in both sets, and the participant’s condition allows, the intensity of the exercise is increased. Conversely, the intensity is reduced if the participant does not reach the minimum number of repetitions or in case of health problems. After the resistance training component, participants perform 20 min of continuous aerobic training, comprised of step aerobics at a moderate intensity (65–75% of age-predicted maximal heart rate; RPE 12–13). The intensity is monitored with the activity tracker and the RPE scale. Finally, a 5–10 min cool down consisting of stretching exercises is performed to conclude each session.

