#### Physical fitness tests (in-person)

The order of the in-person physical fitness tests is standardized. First, we assess balance and functional mobility and subsequently, functional and maximal muscle strength, aerobic capacity and maximum short exercise capacity (Table 3). All tests are performed according to standardized protocols. These protocols can be found in *Additional file 3*.

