As the participant’s most burdensome side effect will differ between participants, inference for this primary endpoint in the whole study sample will be based on a pooled estimate of the stratum-specific standardized mean differences. A two-step procedure will be used. First, standardized ES will be calculated in the four strata separately (e.g., for all patients with fatigue as main side effect, an ES will be calculated). Subsequently, these four standardized ES’s will be pooled using a fixed-effect meta-analytic model. This pooled standardized ES can be interpreted as a stratum-size weighted average of the standardized ES for participant’s most burdensome side effect at 12 weeks.

The same analysis as for HRQoL will be performed for secondary outcomes assessed at more than 2 time points. Outcomes assessed at only two time points (i.e., physical fitness and performance) will be analyzed as between-group differences in outcomes using ANCOVA, adjusted for baseline values and stratification factors. All secondary analyses will be considered exploratory with statistical testing being done at the 5% significance level. For all secondary outcomes, ESs and 95% CIs are reported without *p*-values, according to the European Medicines Agency (EMA) guidelines. The statistical analysis plan is included in the IRB study protocol.

To assess whether a similar intervention effect is seen in the whole study sample or whether subgroups can be identified that benefit most from the intervention, potential moderators of the exercise effect will be investigated, e.g., for main side effect groups, sex, cancer type, or baseline fitness level. Further, to explore potential underlying mechanisms (e.g., inflammation) of exercise effects on the primary outcomes, mediation analyses will be performed.

Missing values of the primary outcome variables as well as all other patient-reported outcomes will be assumed to be Missing at Random (MAR) for primary analyses and dealt with using mixed models for repeated measures (HQRL) and multiple imputation (most burdensome side effect). Intercurrent events (e.g., death, cancer recurrence, non-adherence (i.e., < 80% of scheduled sessions due to external reasons), contamination) will be handled according to our study protocol.

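### The 24-hour rule before blood sampling bars only vigorous exercise, so it can allow a LION session shortly before the week-12 draw, in the intervention arm only

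*Protocol article*

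**What the plan says.** All places are in the protocol article.

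- **Blood markers** fixes the timing: "Blood sampling is performed by vein puncture at baseline and 12 weeks post-baseline". The exercise rule is: "In the 24 h prior to blood sampling, participants are instructed not to exercise vigorously or drink alcohol".
- **Live-remote exercise program** gives three sessions a week for 12 weeks: two Base Module sessions and one Specific Module session. The program starts after the baseline visit, randomization and an individual intake session.
- **Base module—HRQoL** describes the aerobic block as "step aerobics at a moderate intensity (65–75% of age-predicted maximal heart rate; RPE 12–13". The resistance block is labelled moderate-to-vigorous, RPE 13–17.
- **The Specific Module sections** for fatigue, emotional distress and CIPN give no intensity label. For low physical functioning, the third session is another Base Module session.
- **Wait list control group** asks controls to keep their current activity level and starts their program only after the 12-week assessment.
- **Statistical analysis** names the use of the markers: "to explore potential underlying mechanisms (e.g., inflammation) of exercise effects on the primary outcomes, mediation analyses will be performed". It classes all secondary analyses as exploratory.

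**The concern.** The 24-h rule shows that the protocol itself treats recent exercise as a disturbance to the blood samples. The rule is set at vigorous exercise, while most of what the trial delivers is labelled below that level or not labelled at all. A site that follows the wording can let an intervention participant attend a session the day before, or even the day of, the week-12 draw.

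This matters because scheduled sessions before week 12 exist in one arm only. Randomization does not balance an exposure that allocation itself creates. Baseline adjustment does not help either, since neither arm has LION sessions before the baseline draw. If a session produces a short-lived change in the markers, the week-12 difference between arms contains that change as well as any lasting adaptation. A mediation analysis would then count both as the training pathway, and the mixture could hide or imitate an effect on inflammation.

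**Working it through.** The article states no figure on this point, so there is none to reproduce. The check has three parts.

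**1. Are sessions still running at the draw?** The draw is timed from baseline, at 12 weeks. The program also lasts 12 weeks and begins after the baseline visit, randomization and the intake session. A participant seen on schedule is therefore still training or has only just finished. The article states no minimum interval between the last session and the visit.

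**2. How often would a draw fall within 24 h after a session?** Inputs: *k* sessions a week that the rule does not bar, a window of 24 h, and 168 h in a week. Assumptions: sessions still running, all sessions attended, sessions at least 24 h apart, and draw time unrelated to session times. Then

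share = *k* × 24 / 168.

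| Reading of the rule | Stratum | *k* | Share |
|---|---|---|---|
| No LION session counts as vigorous | All | 3 | 72/168 = 43% |
| Base Module sessions count as vigorous | Fatigue, distress, CIPN | 1 | 24/168 = 14% |
| Base Module sessions count as vigorous | Low physical functioning | 0 | 0% |

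The range from 0% to 43% comes entirely from how a site reads one word. Missed sessions, or a program that has already ended, lower these shares. Booking practice could move them either way.

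**3. What would that do to the arm difference?** If a share *p* of the intervention arm carries a transient shift of *s* standard deviations, the week-12 difference moves by *p* × *s*. The documents give no value for *s*. For illustration only, assume *s* = 0.1 to 0.3:

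- *p* = 14%: 0.14 × 0.1 = 0.014 SD to 0.14 × 0.3 = 0.042 SD
- *p* = 43%: 0.43 × 0.1 = 0.043 SD to 0.43 × 0.3 = 0.129 SD
- *p* = 0%: no shift

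These values show how the bias scales. They do not estimate its size.

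**The case against.** The strongest reply is that a sensible site would treat a Base Module session, with resistance work up to RPE 17, as vigorous and keep it out of the 24 h before the draw. Only one mind-body or balance-type session a week would then remain, and in one stratum none. The affected analyses are exploratory, inflammation is named only as an example of a mechanism, and no acute effect size is documented. All of this stands and limits the size of the point. It does not remove the ambiguity, since sites in six countries have to interpret the same word.

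A second reply is that controls are not free of exercise. Table 1 excludes only people above 150 min/week of moderate-to-vigorous exercise, and controls are asked to keep their habits. Either arm may therefore exercise moderately the day before either draw. This also stands. The one-arm contrast holds for LION sessions, while for exercise in general the arms differ in degree.

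A reader might go further and infer that the fitness tests at the same visit contaminate the samples. The baseline visit is described as "assessment of anthropometrics and physical fitness/performance, and blood draw", Study outcomes says "During the in-person visits, anthropometrics and physical fitness/performance are assessed and blood samples are drawn", and the test sequence runs "First, we assess balance and functional mobility and subsequently, functional and maximal muscle strength, aerobic capacity and maximum short exercise capacity". The documents do not support that inference. These are lists of visit content and do not place the blood draw in a sequence. The article adds "All tests are performed according to standardized protocols" and refers to an additional file that is not shown. Under Table 3 both arms take the tests at both baseline and week 12, so the tests create no difference between arms by design.

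**Conclusion.** The point holds as a limited, inexpensive improvement. As worded, the pre-draw rule does not clearly cover the exercise that the trial itself delivers, and the resulting exposure to scheduled sessions falls on one arm at one time point. Between 0% and 43% of intervention-arm draws could fall within 24 h of a permitted session, depending on stratum and on how *vigorously* is read. This assumes running sessions, full attendance and booking unrelated to sessions.

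Two stronger conclusions might be inferred and should not be. The documents show that acute and lasting effects can be mixed. They do not show that this happens, or that any bias is material. Nor does the point reach the primary outcomes, which are questionnaire scores. Only the exploratory blood-marker and mediation analyses are concerned. The documents also give no basis for a window longer than the 24 h they already use.

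**What to change.** 1. In Blood markers, keep the 24-h window but extend it to any LION session and to moderate-to-vigorous exercise, for both arms and both draws. Table 1 already uses the moderate-to-vigorous category.
2. Derive hours since the last attended session for each week-12 draw. Adherence says attendance is documented for every scheduled session, so this can also cover samples already taken, provided the clock time of the draw is available.
3. Repeat the blood-marker and mediation analyses without draws taken within 24 h of a session, as a sensitivity analysis. It should not replace the main analysis, because the exclusion depends on events after randomization and removes intervention-arm samples only.

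Cost: slightly less flexibility in booking the 12-week visit, one wording change, and one derived variable. The sensitivity analysis loses precision. At the 43% share and the 140 per arm that the sample-size section expects after drop-out, it would drop about 140 × 3/7 = 60 intervention-arm draws and leave 80. Applying the extended rule at the remaining visits reduces that loss.
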